## Abstract

**Background:**

Cooling may reduce infarct size and improve neurological outcomes in patients with ischaemic stroke. In phase II trials, cooling awake patients with ischaemic stroke has been shown to be feasible and safe, but the effects in functional outcomes has not yet been investigated in an adequately sized randomised clinical trial.

**Methods/design:**

The EuroHYP-1 trial is a multinational, randomised, superiority phase III clinical trial with masked outcome assessment testing the benefits and harms of therapeutic cooling in awake adult patients with acute ischaemic stroke. The outcomes dealt with here include the *primary outcome* the Rankin score (mRS) at day 91 +/-14 days after randomisation. The *secondary and exploratory outcomes* at day 91 +/-14 days unless otherwise stated encompassing: (1) death or dependency, defined as mRS score > 2; (2) death; (3) National Institutes of Health Stroke Score; (4) brain infarct size at 48 +/-24 hours; (5) EQ-5D-5 L score, and (6) WHODAS 2.0 score. Other outcomes are: the *primary safety outcome* serious adverse events; and the incremental cost-effectiveness, and cost utility ratios. The *analysis sets* include (1) the intention-to-treat population, and (2) the per protocol population. The sample size is estimated to 800 patients (5% type 1 and 20% type 2 errors). All analyses are adjusted for the protocol-specified stratification variables (nationality of centre), and the minimisation variables. In the analysis, we use ordinal regression (the primary outcome), logistic regression (binary outcomes), general linear model (continuous outcomes), and the Poisson or negative binomial model (rate outcomes).

**Discussion:**

Major adjustments compared with the original statistical analysis plan encompass: (1) adjustment of analyses by nationality; (2) power calculations for the secondary outcomes; (3) to address the multiplicity problem using of a fixed-sequence testing procedure starting with the primary outcome followed by the secondary outcomes ordered according to falling power; (4) assignment of worst possible score to patients who are not alive at the planned date of measurement of the continuous scores; (5) improved imputations; (6) outline of a supplementary exploratory analysis of the temperature measurements and time to death; and (7) substantial reduction of sample size.

**Trial registration:**

Clinicaltrials.gov, identifier: NCT01833312. 4 April 2013.

**Electronic supplementary material:**

The online version of this article (doi:10.1186/s13063-017-2302-z) contains supplementary material, which is available to authorized users.

## Introduction

The EuroHYP-1 trial is a multicentre, randomised, superiority phase III international clinical trial with masked outcome assessment testing the benefits and harms of therapeutic cooling in awake adult patients with acute ischaemic stroke (website: http://www.eurohyp1.eu). The trial is designed according to the SPIRIT guidelines, and the background, design, and rationale have previously been published [1]. The EuroHYP-1 trial protocol has been available online on www.ClinicalTrials.gov since the start of the trial on 4 April 2013. The trial is endorsed and supported by European Clinical Research Infrastructures Network (ECRIN) (www.ecrin.org).

Here we describe the updated detailed statistical analysis plan that has been finalised while data collection in the EuroHYP-1 trial is underway, and to which all data analyses in the main publication of the EuroHYP-1 trial results will adhere. A detailed statistical analysis plan was part of the protocol, and the Steering Group of the EuroHYP-1 trial unanimously approved the statistical analysis plan on 30 March 2016. The present amendments of the original statistical analysis plan focus on the primary and the secondary outcomes. The amendments have been made in order to make the analysis more concrete and transparent. Patient recruitment of 800 patients is expected to be completed, and the final follow-up is predicted to occur in 2018–19, after which the database will be locked and data will be analysed.

## Methods

### Objective of the EuroHYP-1 trial

The primary aim of the EuroHYP-1 trial is to determine whether systemic cooling to a target temperature of 34–35 °C, started within 6 hours of onset of stroke and maintained for up to 12 hours thereafter, improves outcomes in patients with acute ischaemic stroke. Inclusion and exclusion criteria are described in the design article in Tables 1 and 2 [1].

**Table 1 Tab1:** Baseline characteristics of the participants in the EuroHYP-1 trial

Baseline characteristics	Intention-to-treat population		Per protocol population	
	Intervention group	Control group	Intervention group	Control group
Centre				
- name of centre 1, N (%)				
- name of centre 2, N (%)				
- name of centre 3, N (%)				
- etc				
Intention to perform thrombolysis, N (%)				
Surface cooling, N (%)				
Males, N (%)				
Stroke severity (NIHSS), mean (SD), N				
Age ≤ 65 years, N (%)				
Age, mean (SD), N				
Visible ischaemic lesion on brain imaging, N (%)				
Time since symptom onset, N ≤ 4 hours (%)				

*NIHSS* National Institutes of Health Stroke Score, *SD* standard deviation

**Table 2 Tab2:** Power (based on an α = 0.05) of the secondary outcomes and serious adverse events provided inclusion of 800 patients into the EuroHYP-1 trial

Outcome	Proportion or mean value in control group	Standard deviation in the control group for continuous outcome	Minimal relevant intervention effect - absolute risk reduction relative to control group	Power
Score of NIHSS at 91 +/-14 days (sample size = 800)	8 points^a^	5 points^a^	2 points^a^	1.00
Serious adverse events at 91 +/-14 days (sample size = 800)	20%	NR	10%	0.98
Death or dependency, defined as modified Rankin score > 2 at 91 +/-14 days (sample size = 800)	63%	NR	7.25%	0.55
Brain infarct size at 48 +/-24 hours (sample size = 800)	10 ml^a^	15 ml^a^	2 ml^a^	0.47
EQ-5D-5 L score at 91 +/-14 days (sample size = 800)	0.50 points	0.40 points	0.05 points	0.42
Death at 91 +/-14 days (sample size = 800)	17%	NR	3.84%	0.33

*NIHSS* National Institutes of Health Stroke Score, *EQ-5D-5 L* EuroQoL quality-of-life scale, *NR* not relevant

^a^Assumed values

The null hypothesis is that there is no difference in death and disability as defined by a score on the modified Rankin Score (mRS) scale measured at 91 +/- 14 days after randomisation of the patient.

For an overview of patient schedule and data collection see Fig. 1.

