### Adjusting variables

The randomisation is stratified according to the nationality of the participating centres and, within each stratum, the patient allocation is based on probabilistic minimisation (80:20) using the following factors:Intention to perform thrombolysis (yes compared to no).Method of cooling (surface compared to endovascular).Sex (male compared to female).Stroke severity (National Institutes of Health Stroke Score (NIHSS)) 6–12 compared to 13 or higher).Age (≤ 65 years compared to > 65 years).Visibility of a relevant ischaemic lesion on the first brain imaging (yes compared to no).Time since symptom onset (≤ 4 hours compared to 4–6 hours).

The primary analyses will be adjusted by the protocol-specified stratification variable country and the seven minimisation factors.

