### Statistical analyses

#### Analytical principles

Analyses will be conducted according to the intention-to-treat principle [2] if not otherwise stated.

All primary tests of significance will be two-sided with alpha = 5%. Analyses will be conducted blinded with the two intervention groups coded as, e.g. 0 and 1. Two conclusions will be drawn, one assuming 0 is the intervention group and 1 is the control, and one assuming the opposite. After two abstracts with two conclusions have been written and both accepted by the Steering Group, the code will be broken.

The primary analyses of primary, secondary, and exploratory outcomes will be those of the intention-to-treat population adjusted for the protocol-specified stratification variable and the minimisation variables, and if necessary using data sets generated using multiple imputation.

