Brain infarct size 48 ± 24 hours after randomisation: assuming a minimal relevant difference of 2 ml, a SD of 15 ml [10], an α of 0.05, and a sample size of 250 participants, the power may then be calculated to 0.18. Accordingly, this outcome will be exploratory.

Number of patients with at least one serious adverse events 91 ± 14 days after randomisation: assuming a control group event proportion of 20% of patients with at least one SAE, an intervention group event proportion of 10% [11], an α of 0.05, and a sample size of 800 participants, the power may then be calculated to 0.98.

Mean number of SAEs per patients: As we do not have prior data to indicate a probable minimal relevant difference, we cannot calculate power for this outcome. These data will be analysed as an exploratory outcome.

The results of calculations of the power are all shown in Table 2. These results are used to determine the sequence in which the secondary outcomes should be tested using the fixed-sequence approach, i.e. the sequence will be as follows:Score on NIHSS at outcome assessment in the period day 91 ± 14 days after randomisation.Proportion of participants with at least one serious adverse event (SAE) until outcome assessment in the period day 91 ± 14 days after randomisation.Death or dependency, defined as a score on the mRS > 2 at outcome assessment in the period day 91 ± 14 days after randomisation.Brain infarct size at imaging assessment in the period 48 ± 24 hours after randomisation.EQ-5D-5 L score at outcome assessment in the period day 91 ± 14 days after randomisation.Death at outcome assessment in the period day 91 ± 14 days after randomisation.

The exploratory outcomes are:WHODAS 2.0 score at outcome assessment in the period day 91 ± 14 days after randomisation.Number of SAEs per patient until outcome assessment in the period day 91 ± 14 days after randomisation.

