#### Multiplicity

We cannot claim a significant beneficial effect of the intervention in the trial if the primary outcome is neutral and a secondary outcome is statistically significant. Therefore, any testing addressing the multiplicity problem must not reduce the power of the test of the primary outcome as compared to the situation where we declare the secondary outcomes exploratory and only test the primary outcome using α = 0.05. Consequently, the primary outcome must be tested initially and using α = 0.05. These requirements may be fulfilled if we use a pre-specified testing sequence (fixed-sequence procedure) where each outcome is tested at α = 0.05 [12]. However, as soon as a non-significant result is obtained, the testing is stopped. However, for exploratory purposes we will calculate the *P* values of the remaining tests and present them. We will use the fixed-sequence procedure starting with the primary outcome and followed by the secondary outcomes, and the exploratory outcomes ordered according to descending power (see Table 2).

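### Table 2 gives stand-alone powers without saying so; under the fixed-sequence rule the chance of declaring NIHSS or SAE is capped at 0.80, and the last three outcomes may fall well below the printed figures.

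*SAP article*

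**What the plan says.** Table 2 (section on the objective of the trial) is captioned as power at α = 0.05 "of the secondary outcomes and serious adverse events provided inclusion of 800 patients into the EuroHYP-1 trial". It prints NIHSS 1.00, SAE 0.98, mRS > 2 0.55, infarct size 0.47, EQ-5D-5 L 0.42 and death 0.33.

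The section on the power of the original secondary outcomes derives these values one outcome at a time and states their use: "These results are used to determine the sequence in which the secondary outcomes should be tested using the fixed-sequence approach".

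The Multiplicity section sets the decision rule: "We will use the fixed-sequence procedure starting with the primary outcome and followed by the secondary outcomes", in a sequence "where each outcome is tested at α = 0.05". It adds that "as soon as a non-significant result is obtained, the testing is stopped"; P values after that point are shown for exploratory purposes only.

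For the primary outcome the abstract says: "The sample size is estimated to 800 patients (5% type 1 and 20% type 2 errors". That is a power of 0.80.

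The text and Table 2 disagree on infarct size. Table 2 has 800 patients and 0.47, and the outcome is fourth in the listed sequence. The text has 250 participants and 0.18, and calls the outcome exploratory.

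**The concern.** A reader who sees one column headed as power, beside a fixed-sequence rule introduced by the same amendment, will take the column as the chance that the trial can claim each outcome. Under the rule that chance is the probability that the outcome and everything before it are significant, which is generally smaller. Nothing in the article says that the printed figures leave out the gates. The Discussion likewise gives probabilities of missing a mortality difference without mentioning that death comes last in the sequence.

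What is at stake is interpretation. If a late outcome is not declared, someone relying on Table 2 will underestimate how likely that was even with every assumed effect true, and may read too much into it. The type 1 error is not affected.

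**Working it through.** **Inputs.** N = 800 and primary power 0.80 (abstract); significance level from Analytical principles: "All primary tests of significance will be two-sided with alpha = 5"%; effects and SDs from Table 2 and the power section. The allocation ratio is not printed (the 80:20 under Adjusting variables is the minimisation probability), so 400 per arm is assumed.

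**Step 1: reproduce Table 2 as single tests.**

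Means: power = Φ(δ / (σ√(2/n)) − 1.96), n = 400.
- NIHSS: 2 / (5 × 0.0707) = 5.66; Φ(3.70) = 0.9999 (printed 1.00)
- Infarct size: 2 / (15 × 0.0707) = 1.886; Φ(−0.074) = 0.470 (printed 0.47)
- EQ-5D-5 L: 0.05 / (0.40 × 0.0707) = 1.768; Φ(−0.192) = 0.424 (printed 0.42)

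Proportions: power = Φ((d − 1.96·SE₀) / SE₁), with SE₀ pooled and SE₁ unpooled.
- SAE, 0.20 v 0.10: (0.1000 − 0.0495) / 0.0250 = 2.02; 0.978 (printed 0.98)
- mRS > 2, 0.63 v 0.5575: (0.0725 − 0.0681) / 0.0346 = 0.13; 0.551 (printed 0.55)
- Death, 0.17 v 0.1316: (0.0384 − 0.0496) / 0.0253 = −0.44; 0.329 (printed 0.33)

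All six reproduce, with no allowance for earlier tests. The text's infarct figure also reproduces with 125 per arm: 2 / (15 × 0.1265) = 1.054; Φ(−0.906) = 0.18.

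**Step 2: apply the sequence.** P(outcome k declared) = P(primary and outcomes 1 to k all significant).
- Ceiling: the smallest power in the chain up to k. It needs no correlation assumption and is reached under perfect dependence.
- Independence: the product. 0.80 × 1.00 = 0.80; × 0.98 = 0.784; × 0.55 = 0.431; × 0.47 = 0.203; × 0.42 = 0.085; × 0.33 = 0.028.
- In between: 1,000,000 draws of equicorrelated normal test statistics, with means set to give the printed powers and 0.80 for the primary. The correlation ρ is an assumption.

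| Outcome, in order | Printed | Independence | ρ = 0.5 | ρ = 0.7 | Ceiling |
|---|---|---|---|---|---|
| NIHSS | 1.00 | 0.80 | 0.80 | 0.80 | 0.80 |
| SAE | 0.98 | 0.78 | 0.79 | 0.80 | 0.80 |
| mRS > 2 | 0.55 | 0.43 | 0.50 | 0.52 | 0.55 |
| Infarct size | 0.47 | 0.20 | 0.32 | 0.37 | 0.47 |
| EQ-5D-5 L | 0.42 | 0.09 | 0.22 | 0.28 | 0.42 |
| Death | 0.33 | 0.03 | 0.14 | 0.20 | 0.33 |

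**Step 3: the infarct-size conflict.** If 0.18 applies at step 4, infarct size, EQ-5D-5 L and death all have a ceiling of 0.18; under independence they are 0.431 × 0.18 = 0.08, × 0.42 = 0.03 and × 0.33 = 0.01. If infarct size leaves the chain as exploratory, independence gives EQ-5D-5 L 0.431 × 0.42 = 0.18 and death 0.181 × 0.33 = 0.06, with ceilings of 0.42 and 0.33.

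**The case against.** The best defence is that Table 2 never claims to show power under the sequence. The powers were calculated to order the tests, stand-alone power is a legitimate basis for that, and the stopping rule is written out for anyone to apply. The plan is also open about low power for mortality: the Discussion says that differences of 5% or less are likely to go undetected. Risk ratios with 95% CIs are already promised for the binary outcomes.

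Most of this stands. A reader might infer that Table 2 is miscalculated or that the order is wrong. The documents support neither: every value reproduces, and the ordering use is stated.

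A reader might also take the independence column as the expected result and conclude that the late outcomes are almost certain not to be declared. That goes too far. mRS > 2 and death are cut-points of the primary scale, and patients who die receive the worst score on the continuous outcomes, so the tests are related and independence is a pessimistic limit. At ρ = 0.5 the chance of declaration is still about 0.22 for EQ-5D-5 L and 0.14 for death, and at ρ = 0.9 it is 0.36 and 0.28. For mRS > 2 the loss is small.

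The defence does not remove the missing label, the ceiling of 0.80, or the lack of any planned effect estimate with CI in Table 5.

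**Conclusion.** The point holds as an unlabelled power that overstates what the decision rule delivers. It is not an arithmetic error.

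For NIHSS and SAE the overstatement is certain given the stated 0.80 for the primary: 1.00 − 0.80 = 0.20 and at least 0.98 − 0.80 = 0.18. For the other four its size depends on correlations that the article does not give. It is small for mRS > 2 and, at moderate correlation, material for infarct size (0.47 to about 0.32), EQ-5D-5 L (0.42 to about 0.22) and death (0.33 to about 0.14). The printed values for these four are reached only under perfect dependence.

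The figures assume 400 per arm, Table 2's effects and its 0.47 for infarct size. They also take the primary power of 0.80 at face value; its basis at 800 patients is left to protocol version 4, which is not shown, and a lower primary power would lower the ceiling for NIHSS and SAE by the same amount.

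**What to change.** 1. Reconcile the infarct-size entry first: Table 2 (800 patients, 0.47, fourth in the sequence) against the text (250 participants, 0.18, exploratory). The later figures depend on it.
2. In Table 2, rename the column 'stand-alone power (single two-sided 5% test)'.
3. Add a column for the probability of declaration under the fixed sequence, giving the independence value, the perfect-dependence ceiling, and a simulation at stated correlations.
4. In the Multiplicity section and Table 5, commit to an effect estimate with 95% CI for every outcome, including those not reached, and state that an outcome not reached is not evidence of no effect.

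The test order and alpha do not change. The cost is some SAP wording and a short simulation; the only downside is that the stated chances look less favourable.

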**Fig. 1 Fig1:**
[figure not shown]
Overview of patient schedule and data collection in the EuroHYP-1 trial (*grey tone* only for the experimental group). 1 Re-warming: hypothermia group only. 2 Previous medication including alteplase. 3 Includes sodium, potassium, magnesium, creatinine, urea, gamma-glutamyl transpeptidase, ASAT, ALAT, alkaline phosphatase, blood glucose; haemoglobin, haematocrit, erythrocytes, leukocytes, platelets, INR. Further samples may be taken throughout the study at the discretion of the investigator. 4 Body temperature will be assessed according to local clinical practice with tympanic, bladder, or rectal temperature measurement, except in patients randomised to therapeutic hypothermia from start of treatment phase (TP, beginning of hour 1) until end of re-warming period, when bladder or rectal thermal probes will be used. During TP, body temperature will be assessed every 15 min during the first 3 hours (except at time points t = 0 min and t = 15 min) and every 60 min thereafter in patients randomised to therapeutic hypothermia, every 60 min (except at time point t = 0 min) in patients randomised to best medical treatment alone, subsequently in all patients at 8-hour intervals until A6 (day 8 or day of discharge from hospital, whichever occurs first). 5 The mRS assessment at outcome assessment (A7) will be recorded using a digital video camera. The clip will then be transferred to the EuroHYP-1 outcome adjudication web portal. 6 Anti-shivering medication: induction: buspirone 10 mg p.o./pethidine 50 mg i.v. (2 min); repeat doses of 10 mg buspirone p.o. may be administered as long as a maximum dose of 30 mg/24 h is respected; a bolus of pethidine 25 mg i.v. may be given as long as an interval of at least 30 min is respected and a maximum dose of 500 mg/24 h is not exceeded. 24 h-doses include induction bolus. For the prevention and treatment of opioid-induced nausea and vomiting, a 5HT3RA may be administered as support medication. 7 Induction of cooling: 20 ml/kg estimated bodyweight 4 °C isotone saline or Ringer´s lactate over a period of 30–60 min; EMCOOLS Brain.Pad, if available. 8 IMDs permitted for cooling: EMCOOLS Brain.Pad (for induction of cooling only); Medivance/Bard Arctic Sun temperature management system with heat exchange control unit Arctic Sun 2000 or Arctic Sun 5000 and ArcticGel Pads; MTRE CritiCool temperature management system with heat exchange control unit CritiCool, accessoires and CureWrap; Zoll IVTM system with heat exchange control unit CoolGard 3000 or Thermogard XP, CoolGard start-up kit and intravascular temperature management catheters ICYy 3893 AE or ICY 3893 CO. 9 If endovascular cooling is performed, the catheter insertion site must be visually inspected for detection of bleeding/haematoma in 3-hour intervals during TP and once 3 hours after removal of the intravascular catheter. 10 Monitoring for pneumonia includes monitoring of oxygen saturation and body temperature, physical examination (auscultation, percussion) and, if clinically indicated, chest X-ray. Monitoring for signs of pneumonia must be performed from screening assessment (A1, within 90 minutes before the start of the treatment phase TP) until A6 (day 8 or day of discharge from hospital, whichever occurs first). 11 Patient location during stay in hospital must be assessed at 12:00 hours on each day in hospital. 12 WHODAS 2.0 questionnaire and EQ-5D questionnaire must be filled in by the patient or his/her relative/carer at outcome assessment (A7). 13 Health Recovery Guide and Diary: Section 6: filled in by the patient every day from discharge to V7; Section 7: filled in by the carer/relative prior to V7. 14 For participation in the biomarker sub-study a special informed consent form must be filled in by the patient or his/her legal representative. Assessment at End of Hour 24 ± 2 hours. 15 Only selected study sites. 16 Informed consent will be obtained in accordance with national regulatory requirements. 17 NIHSS assessment at End of Hour 24 ± 2 hours. 18 Starting at t = 30 min. 19 Every 60 minutes only. 20 Prior to intended repeat administration of pethidine. *CT* computed tomography, *ECG* electrocardiogram, *EQ-5D-5 L* EuroQoL quality-of-life scale, GCS Glasgow coma scale, *MRI* magnetic resonance imaging, *NIHSS* National Institutes of Health Stroke Score, *SAE* serious adverse event, *WHODAS* World Health Organization Disability Assessment Schedule

### The sample size

Originally, we planned to demonstrate or reject an absolute difference of 7% between the intervention groups (equivalent to an odds ratio (OR) of 0.74) and allowing for 3% loss to follow up in a sample size of 1500 randomised patients with a type 1 error risk of 5% and a type 2 error risk of 10% (EuroHYP-1, EudraCT number 2012-002944-25, version 2, 20 December 2012). Due to exceptionally slow enrolment, we realised that this target was no longer realistic. Accordingly, in 2014, the sample size was downgraded to 800 patients based on considerations explained in version 4 of the protocol (EuroHYP-1, EudraCT number 2012-002944-25, European Database on Medical Devices (EUDAMED) number CIV-12-09-008821, planned trial period July 2013 to March 2017 (45 months), version 4, date 29 June 2015). Currently, the project has been prolonged until 31 July 2018.

